### Study population

The Ministry of Education (MOE) Malaysia will supervise this study. The participants will be Standard 4 and Form 4 students from primary and secondary government schools, respectively, in Selangor and Kuala Lumpur. There are 661 primary schools and 279 secondary schools in Selangor, and 218 primary schools and 125 secondary schools in Kuala Lumpur. The schools include national, technical, science, religious, and boarding schools [19].

### Inclusion and exclusion criteria

The school inclusion criteria in this study are presented as follows: i) Selangor and Kuala Lumpur primary and secondary schools, ii) MOE-supervised government school, and iii) MOE permission. The exclusion criteria are presented as follows: i) school for special needs students, and ii) the distance between selected schools < 10 km.

The participants inclusion criteria are presented as follows: i) Malaysian citizen, ii) Standard 4 or Form 4 student, iii) parent or caregiver consent for student’s participation, and iv) school consent. The participants exclusion criteria are presented as follows: i) unable to read Bahasa Malaysia or English, ii) physically or mentally impaired and holding a disability card, and iii) temporary student (< 6 months at the involved school) during the study period.

### Sample size estimation

The sample size was calculated based on the desired primary outcome, namely knowledge of dengue prevention and control. The sample size was calculated using the formula for testing the difference in proportions between two groups [20]. Adjustment for a 70% attrition rate established that the sample size required for this study is 800 pairs of intervention and control groups, which amount to 1600 participants.

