**Methods:**

This study is a single-blinded, cluster randomised controlled trial to be conducted from 1 September 2023 to 31 August 2025. The study will involve 20 primary and 20 secondary schools in Selangor and Kuala Lumpur. The 1600 participants will be randomly allocated to intervention and control groups based on selected clusters to avoid contamination. A cluster is a comparable school that fulfils the inclusion and exclusion criteria. The intervention group will receive the iDEAL module, while the control group will receive standard education. The iDEAL module will be developed following a systematic procedure and delivered in-person by trained researchers to the participants. The outcome will be measured using validated, self-administered questionnaires at baseline (T_0_), immediately (T_1_), one month (T_2_), and three months (T_3_) post-intervention to measure the intervention module effectiveness. The data will be analysed using IBM Statistical Package for Social Science (SPSS) version 28 and descriptive and inferential statistics. Within-group changes over time will be compared using one-way repeated measure analysis of variance for continuous and normally distributed variables. Within-group analysis of categorical data will use Cochran’s Q test. The main effect and interaction between and within the intervention and control groups at T_0_, T_1_, T_2_, and T_3_ will be tested using the generalised linear mixed model (GLMM). Hypothetically, the KAP, environmental cleanliness index, and dengue index among the intervention group will be significantly improved compared to the control group. The hypothesis will be tested using a significance level with a p-value of 0.05 and a confidence interval of 95%.

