### Sampling method and participant recruitment

This study will use multistage sampling. The first sampling stage will use proportionate simple random sampling to select 40 schools based on the Selangor and Kuala Lumpur districts. There are nine districts in Selangor and 11 districts in Kuala Lumpur. Thus, all 20 districts in Kuala Lumpur and Selangor will be included for the proportionate simple random sampling to select 40 schools. The school selection sampling frame will be the list of Selangor and Kuala Lumpur schools according to primary and secondary schools from 20 districts. For this exercise, the sampling frame A will consist of primary school while sampling frame B will consist secondary school. This sampling frame to ensure the required 20 schools for Standard 4 (primary school) and 20 school from Form 4 (secondary school) can be obtained. In the second sampling stage, one classroom from each school selected from the first sampling stage will be chosen using simple random sampling. These samplings will yield 20 Standard 4 classrooms and 20 Form 4 classrooms. Subsequently, the sampling frame will be the Standard 4 and Form 4 classroom list from each selected school. All students in the selected classrooms will be invited to participate in the study.

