### Randomisation

School cluster randomisation will be used to ensure administrative efficacy, reduce risk of experimental contamination, and enhance participant compliance. The Standard 4 and Form 4 classrooms will be randomly divided into intervention and control groups. The randomisation unit will be 1:1 in the control or intervention group. Contamination due to geographical issues will be minimised by setting the distance between each school to a minimum of 10-km radius from each other. A school will be randomly reselected from the sample frame to replace any school that does not fulfil this criterion.

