### Sequence generation

Upon recruiting the schools and participants that fulfil the eligibility criteria, schools will be allocated to intervention or control groups using permuted block randomisation. The approach will ensure that closely balanced numbers of schools will be allocated to each study arm. Variable block sizes of 4, 6, and 8 will be used to blind the researcher from predicting the school allocation process.

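### The required 1600 participants are derived from an individual-level two-proportion formula with attrition as the only named adjustment, although 40 whole schools are randomised

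*Protocol article*

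**What the plan says.** The Sample size estimation section sets out a short chain. The outcome comes first: "The sample size was calculated based on the desired primary outcome, namely knowledge of dengue prevention and control". The method follows: "The sample size was calculated using the formula for testing the difference in proportions between two groups [20". Then comes the only inflation named: "Adjustment for a 70% attrition rate established that the sample size required for this study is 800 pairs of intervention and control groups". The total is given as 1600. The section mentions no ICC, design effect, class size or number of schools.

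The design is clustered. The abstract's Methods paragraph says "This study is a single-blinded, cluster randomised controlled trial to be conducted from 1 September 2023 to 31 August 2025" and gives 20 primary and 20 secondary schools. Under Randomisation, "School cluster randomisation will be used to ensure administrative efficacy". Under Sequence generation, "schools will be allocated to intervention or control groups using permuted block randomisation". Under Sampling method and participant recruitment, "one classroom from each school selected from the first sampling stage will be chosen using simple random sampling". The abstract calls the cluster a school and Study design calls it a classroom. With one classroom per school the cluster count is 40 either way.

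**The concern.** Pupils in one classroom share teachers, a school programme and local dengue activity, so their knowledge answers are likely to be correlated. A two-group proportion formula assumes independent answers. If its result is inflated for attrition alone and then applied to 20 schools per arm, the effective sample is smaller than the one the formula called for.

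What is at stake is power and the reading of a null result. A reader who takes 1600 as the required size may conclude that the module does not work, when the trial could not reliably have detected the difference it was sized for. This point is about sizing only. How the analysis handles clustering is a separate question.

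**Working it through.** **Inputs from the article.** 1600 enrolled, 800 per arm, 70% attrition (Sample size estimation); 40 schools (abstract, Sampling method); one class per school (Sampling method); 1:1 allocation (Randomisation); significance level 0.05 (Data analysis). Enrolment per class is 1600/40 = 40.

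**Not given, so assumed.** Two-sided test, 80% target power, control proportion p1 = 50%, ICC 0.02 to 0.10, equal class sizes.

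**1. Can 1600 be reproduced?** No, because the two proportions and the power are missing. Working back from 800 per arm, the analysed number depends on how 70% was used:
- as loss, N/(1 − 0.7): 800 × 0.3 = 240 per arm, 240/20 = 12 per class;
- as an add-on, N × 1.7: 800/1.7 = 471 per arm, 23.5 per class;
- as retention, N/0.7: 800 × 0.7 = 560 per arm, 28 per class.

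Ordinary individual-level inputs come close to each of these without a design effect. For example, 35% v 47.5% at 80% power needs 243 per arm; 60% v 70% at 90% power needs 477; 25% v 32.5% at 80% power needs 571. This shows that no design effect is needed to reach about 800. It does not prove that none was used.

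**2. Design effect.** DE = 1 + (m − 1) × ICC, with m the analysed pupils per class. At ICC 0.05:
- m = 12: 1 + 11 × 0.05 = 1.55, effective n per arm 240/1.55 = 155;
- m = 23.5: 1 + 22.5 × 0.05 = 2.125, effective n about 221;
- m = 28: 1 + 27 × 0.05 = 2.35, effective n 560/2.35 = 238.

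**3. Power.** For each n, take the difference d that has 80% power under independence: d = (1.960 + 0.842) × √{[p1(1 − p1) + p2(1 − p2)]/n}. This gives 12.6, 9.1 and 8.3 percentage points. With clustering, the noncentrality is 2.802/√DE, referred to a t distribution on 40 − 2 = 38 df.

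| Analysed per arm (per class) | ICC 0.02 | ICC 0.05 | ICC 0.10 |
|---|---|---|---|
| 240 (12) | DE 1.22, power 70% | DE 1.55, power 59% | DE 2.10, power 47% |
| 471 (23.5) | DE 1.45, power 62% | DE 2.13, power 47% | DE 3.25, power 33% |
| 560 (28) | DE 1.54, power 60% | DE 2.35, power 43% | DE 3.70, power 29% |

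The t reference alone costs about 2 points (80% becomes 78% at ICC 0); the rest is the design effect. With a normal reference, the ICC 0.05 column is about 61%, 49% and 45%.

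**4. Detectable difference.** At ICC 0.05, for 80% power on 38 df, it rises from 12.6, 9.1 and 8.3 to about 15.9, 13.4 and 13.0 percentage points.

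**5. Retention better than planned.** Suppose the target was 240 per arm.
- Full retention, ICC 0.05: effective n is 800/[1 + 39 × 0.05] = 800/2.95 = 271, above 240, and power is about 83%.
- 90% retained, ICC 0.05: power about 81%.
- 70% retained, ICC 0.05: 560/2.35 = 238, power about 78%.
- Full retention, ICC 0.10: 800/4.90 = 163, power about 61%.

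The other readings leave much less slack. Full retention covers a DE of 800/471 = 1.70, so ICC up to 0.70/39 = 0.018, or of 800/560 = 1.43, so ICC up to 0.43/39 = 0.011.

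**6. Schools needed to hold the target.** With 12 analysed per class and a normal reference: 20 × 1.55 = 31 per arm (62 schools) at ICC 0.05, and 20 × 2.10 = 42 per arm (84 schools) at ICC 0.10.

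**The case against.** The strongest reply is that a three-sentence paragraph in a condensed article leaves out much, including the proportions and the power. The full protocol and the cited source of the formula are not shown, so a design effect may sit inside the calculation. This limits what can be said: the article names no design effect, and it cannot be shown that none was applied. It does not rescue the paragraph, which presents the attrition adjustment as the step that produced the required size. If clustering was allowed for, the stated derivation is wrong as a description. If it was not, the size is wrong for the design.

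A second reply is that the generalised linear mixed model in the Data analysis section may deal with clustering. Modelling correlation at the analysis stage does not restore power that was not planned, and the article does not link the model to the sample size.

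A third reply has more force. On the 240-per-arm reading, a 70% loss allowance leaves a large reserve, and ordinary retention would absorb an ICC near 0.05. That stands. But the protection would be accidental, depends on the plan's own attrition figure being far too high, fails at ICC 0.10, and is slight on the other two readings.

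A reader might also set the effective size at full class size against enrolment, for instance 271 against 800 at ICC 0.05. That is the wrong comparison: it assumes no attrition, and 800 is the number enrolled, not the number the formula required.

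**Conclusion.** The point holds in conditional form, and the paragraph needs correcting. The stated route to 1600 ignores clustering in a trial that randomises 40 schools. The direction needs no assumed value: at the planned attrition, any positive ICC puts the design effect above 1 and power below the target. The size does need assumptions. With an 80% target, a 50% control proportion, equal classes and 38 df, power lies between about 70% (ICC 0.02, 240 per arm) and 29% (ICC 0.10, 560 per arm). Unequal class sizes would make this worse; adjustment for the baseline score could recover some of it.

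A reader might infer that the trial is certainly underpowered, or underpowered by a known amount. The article does not support that: it states neither a power nor an ICC, and retention much better than planned could make up the loss on one reading of the 70%.

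**What to change.** Rewrite the Sample size estimation paragraph as a cluster-trial calculation. State both proportions, the target power, the ICC with a sensitivity range (for example 0.02 to 0.10) and the expected number of analysed pupils per class. Multiply the individual-level size by 1 + (m − 1) × ICC, and use a t reference on about 38 df. Then report the power, or the minimum detectable difference, that 20 schools per arm give, and stop describing 1600 as the size required on an individual-level basis. If the planned analysis adjusts for the baseline score, the calculation may take credit for it, with the assumed correlation stated. If a design effect was in fact used, say so and give its value.

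The cost is one paragraph and a less favourable stated power or detectable difference. Keeping the 40 schools means accepting that. Holding the target power at the planned attrition would instead take more schools, about 62 at ICC 0.05 on the 240-per-arm reading.

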### Sampling method and participant recruitment

This study will use multistage sampling. The first sampling stage will use proportionate simple random sampling to select 40 schools based on the Selangor and Kuala Lumpur districts. There are nine districts in Selangor and 11 districts in Kuala Lumpur. Thus, all 20 districts in Kuala Lumpur and Selangor will be included for the proportionate simple random sampling to select 40 schools. The school selection sampling frame will be the list of Selangor and Kuala Lumpur schools according to primary and secondary schools from 20 districts. For this exercise, the sampling frame A will consist of primary school while sampling frame B will consist secondary school. This sampling frame to ensure the required 20 schools for Standard 4 (primary school) and 20 school from Form 4 (secondary school) can be obtained. In the second sampling stage, one classroom from each school selected from the first sampling stage will be chosen using simple random sampling. These samplings will yield 20 Standard 4 classrooms and 20 Form 4 classrooms. Subsequently, the sampling frame will be the Standard 4 and Form 4 classroom list from each selected school. All students in the selected classrooms will be invited to participate in the study.

### Randomisation

School cluster randomisation will be used to ensure administrative efficacy, reduce risk of experimental contamination, and enhance participant compliance. The Standard 4 and Form 4 classrooms will be randomly divided into intervention and control groups. The randomisation unit will be 1:1 in the control or intervention group. Contamination due to geographical issues will be minimised by setting the distance between each school to a minimum of 10-km radius from each other. A school will be randomly reselected from the sample frame to replace any school that does not fulfil this criterion.

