### Study location

The study will be conducted in Selangor and Kuala Lumpur, which are dengue hotspots that recorded the most dengue cases in Malaysia [16]. Selangor (latitude 2° 35’–3° 60’ N, longitude 100° 45’–102° 00’ E) has a land area of 7,945 km^2^ and is one of the most developed and highly populated states in Peninsular Malaysia [17, 18]. Kuala Lumpur (3° 8’ 28.3” N, 101° 41’ 11.5” E) is located on the west coast of Peninsular Malaysia with a land area of 243 km^2^ [17]. In 2020, the Selangor population was 6,994,423 with a population density of 880/km^2^. Children comprised 29.5% of the Selangor population. The Kuala Lumpur population numbered 8,622,000 (population density: 8157/km^2^), which rendered it the most densely populated and urbanised location in Malaysia [17]. Kuala Lumpur is the Malaysian capital and a federal territory in Selangor, which significantly influences its social and economic development. Furthermore, the ecological flows, patterns, and processes of Selangor and Kuala Lumpur are interlinked. Therefore, the analysis will include Kuala Lumpur.

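### The 10-km spacing rule and proportionate sampling cannot both hold in Kuala Lumpur's stated 243 km²; reselection moves Kuala Lumpur places to Selangor

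*Protocol article*

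**What the plan says.** - **Sampling method and participant recruitment:** "Thus, all 20 districts in Kuala Lumpur and Selangor will be included for the proportionate simple random sampling to select 40 schools". Eleven of the 20 districts are in Kuala Lumpur. There are separate frames for primary and secondary schools, and 20 schools are drawn from each.
- **Inclusion and exclusion criteria:** one ground for excluding a school is "the distance between selected schools < 10 km".
- **Randomisation:** contamination is to be limited by "setting the distance between each school to a minimum of 10-km radius from each other". For a school that breaks the rule: "A school will be randomly reselected from the sample frame to replace any school that does not fulfil this criterion".
- **Study population:** "218 primary schools and 125 secondary schools in Kuala Lumpur", against 661 and 279 in Selangor.
- **Study location:** Kuala Lumpur "is located on the west coast of Peninsular Malaysia with a land area of 243 km^2"; Selangor "has a land area of 7,945 km^2".
- **Strengths and limitations:** the 10-km separation is given as one reason why the module's effect can be measured precisely.

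The distance rule covers every pair of selected schools. It is not limited to schools in opposite arms or to schools of the same level.

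**The concern.** Kuala Lumpur holds over a quarter of the eligible schools (343 of 1,283) on about 3% of the land (243 of 8,188 km²). A proportionate draw puts many schools there, and a 10-km exclusion distance allows only a few. If the two rules conflict, the distance rule decides the sample, because it is an exclusion criterion with its own replacement step. The achieved sample would then differ from the one described, and in a known direction: away from the area that the article calls the most densely populated and urbanised in the country and counts among its dengue hotspots. Alternatively, the team would have to waive an exclusion criterion during school selection, with no stated rule for doing so.

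**Working it through.** The article gives no Kuala Lumpur share, so there is no stated figure to reproduce. The check compares the number of schools needed with the number that fit.

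**1. Schools needed in Kuala Lumpur**
- Primary: 20 × 218/(661 + 218) = 4.96.
- Secondary: 20 × 125/(279 + 125) = 6.19.
- Total: 11.1 of 40. Pooling the levels gives 40 × 343/1,283 = 10.7.
- If proportionate means by population, the result depends on which population figure is used. Area × density (243 × 8,157 ≈ 1.98 million) gives 8.8 schools; the stated 8,622,000 gives 22.1.

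**2. Upper limit on the number that fit**

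Inputs: A = 243 km², d = 10 km. Kuala Lumpur's shape is not given, so a reasonably compact (convex) area is assumed.
- Densest packing uses d²√3/2 = 86.6 km² per school, and 243/86.6 = 2.8 before edge effects.
- With edges, Oler's inequality gives N ≤ (2/√3)(A/d²) + P/(2d) + 1, where P is the perimeter.
- Disc (radius 8.79 km, P = 55.3 km): 2.81 + 2.76 + 1 = 6.57, so at most 6. An exact check gives 5: five points 10 km apart need a radius of 8.51 km, and six need 10.0 km.
- Rectangles: 6.9 for a square, 7.1 at 2:1, 8.0 at 5:1.
- Eleven schools would need P ≥ 2 × 10 × (11 − 1 − 2.81) ≈ 144 km, for example a strip of about 68 × 3.6 km.

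Every reading of the share in step 1 (8.8 to 22.1) exceeds every one of these limits up to 5:1.

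**3. What random selection with replacement achieves**

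With 343 schools placed uniformly in a 243 km² disc, selection until no eligible school was left gave 1, 2, 3 or 4 schools in 2%, 9%, 75% and 14% of 20,000 runs. Rectangles from 1:1 to 5:1 averaged 3.0 to 3.3, with a maximum of 5.

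**4. What the stated replacement rule does**

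The frame covers all 20 districts. With uniform placement and Kuala Lumpur set inside Selangor, frame-wide reselection at 10 km reached 40 schools in 300 of 300 runs, with about 2 in Kuala Lumpur on average. Selangor has room: its 7,945 km² has a bound above 100 and random saturation of about 55 by area, against its proportionate share of about 29.

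**5. Distances at which 11 schools fit in 243 km²**

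Uniform placement, 2,000 runs each, disc / 2:1 rectangle:

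| Distance | Runs fitting 11 or more |
|---|---|
| 3 km | 100% / 100% |
| 4 km | about 96% / 98% |
| 5 km | about 1% / 3% |
| 10 km | 0% / 0% |

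**6. Consistency of the area figure**

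The stated population divided by the stated density is 8,622,000/8,157 = 1,057 km², not 243 km². At 1,057 km² the disc bound is about 19, so 11 schools could fit in theory. Random saturation by area would be about 7, and that figure ignores edge effects, so it is on the low side.

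**The case against.** **The replacement rule resolves the conflict.** In part it does. A reader might infer that selection could never finish. That would follow only if replacements had to come from the same district or from Kuala Lumpur, and the article does not say so. It draws them from the sample frame, which spans all 20 districts, and on that reading 40 schools are found. What remains is the displacement of Kuala Lumpur schools.

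**All districts are in the frame, but none is promised a school.** This stands. A reader might infer that at least one school is needed from each of the 11 Kuala Lumpur districts. The text only includes the districts in the sampling, so the point rests on the proportionate share alone.

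**The share of 11 is derived and the shape is unknown.** Both are true. The alternative readings still exceed capacity, and only an extreme strip of about 20:1 would allow 11 even in theory.

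**The area may be wrong.** The population and density figures do imply a larger one, and at 1,057 km² the conflict would be much weaker. The land area is, however, stated outright as 243 km².

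**The trial result is not biased.** This stands. Spacing acts on which schools enter. Allocation by permuted blocks follows recruitment, so the arms remain comparable, and no Kuala Lumpur estimate is planned in the article.

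**Conclusion.** The point holds, and it should be fixed. On the article's own counts and land area, about 11 Kuala Lumpur schools are called for, at most about 6 can be 10 km apart, and about 3 would be reached by random selection within Kuala Lumpur. Under frame-wide replacement about 2 would remain. The sample would therefore not be proportionate as described, and it would under-represent the densest area. The consequence is for representativeness and for the description of the sampling, not for the validity of the between-arm comparison.

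This rests on three assumptions: proportionate means by school count (other readings do not change the direction), Kuala Lumpur is reasonably compact, and 243 km² is the correct area. The simulated figures also assume uniformly placed schools; real coordinates will shift them.

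**What to change.** Reconcile Inclusion and exclusion criteria, Sampling method and participant recruitment, Randomisation, and Strengths and limitations, in one of two ways:

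- **(a) Keep proportionate sampling.** Prespecify one minimum distance that the actual school coordinates can satisfy, applied across both school levels. Spacing only within a level could place a primary and a secondary school from opposite arms next to each other. Step 5 suggests about 3 km, or 4 km with a small risk of falling short. Draw replacements from the same stratum, at least the same state and school level. A same-district rule is tighter: with one school in each of 11 equal districts, selection completed in only 53% to 60% of runs at 4 km and about 99% at 3 km. Restate the 10-km contamination claim to match the chosen distance.
- **(b) Keep 10 km.** Drop the word proportionate, and state that Kuala Lumpur will be under-represented and how far the findings then apply to it.

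In either case, correct whichever of Kuala Lumpur's area, population or density is wrong.

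The cost is wording plus a desk check of school coordinates before the draw. Option (a) brings schools closer together and may add some contamination. The documents do not quantify this, and the introduction expects knowledge to pass from school to home, so the sponsor should justify the distance chosen.
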